### Sample size calculation

2.8

The most important outcome in this study is fasting serum insulin. Sample size was estimated based on the above primary outcome measures. The target sample size calculated by PASS 11.0 is a total of 63 participants (21 participants in the Group A, 21 participants in the Group B, 21 participants in the Group C). This result was based on a power calculation using a 5% significance level, 90% power, and current knowledge of the average serum insulin level. By enrolling 27 participants in each group, we can allow a drop-out rate of 20%.

### Recruitment

2.9

Eligible subjects will be offered a consent form including information on the background, purpose, possible benefits, and harms of the study after detailed consultation and explanation of the study design. Depending upon the provision of consent, patients will be enrolled.

### Randomization and allocation concealment

2.10

Eligible participants will be allocated to the three groups in a 1:1:1 ratio by an investigator according to a random sequence generated by a computer. The random number assignment will be generated by an independent statistician who will not be a member of the research team. The random number will be placed in sealed, opaque envelopes and assigned by a staff, who will not be a member of the clinical trial team and participating in data collection. When new participants are enrolled in the study, the doctor will open the envelopes in sequence and assign participants to the corresponding intervention accordingly. All processes will be recorded and saved as appropriate.

### Blinding

2.11

In this study, patients, research staff, and data statisticians will be blinded to the assignment. However, acupuncture therapists cannot be masked as sham acupuncture will be practiced differently from real acupuncture. Acupuncture therapists will not be allowed to share any information in terms of patient intervention with other researchers, including the data statistician.

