### Interventions

2.6

After baseline measurements, patients satisfying the inclusion criteria will be randomly divided into 1 of the 3 treatment groups, as shown below:

1.Group A: SWJQD combined with acupuncture for 3 months.2.Group B: SWJQD combined with sham acupuncture for 3 months.3.Group C: Metformin at a dose of 500 mg 3 times/day for 3 months.

All the participants will be instructed to return to visit the doctor every week.

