Therefore, we considered whether the combination of Chinese medicine and acupuncture could be more effective in improving levels of the relevant hormones in patients with PCOS. There is a lack of relevant clinical evidence in this regard, which we aim to address in this trial. Thus, we will provide supporting evidence for the combination of traditional Chinese medicine and acupuncture to treat PCOS. Many problems have existed in the quality control of the past randomized controlled trials of in the field of traditional Chinese medicine.^[33]^ In order to ensure the quality of our research, avoid bias, and obtain reliable conclusions, we used randomization and blinding methods by using software to randomly generate sequences and conceal random numbers. The limitations of this study are that the sample size is small, and the blinding method cannot be completely used for the acupuncture therapist. Nevertheless, we expect that this study will be able to provide some new evidence regarding traditional Chinese medicine and acupuncture in the treatment of PCOS.

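### Section 2.11 claims blinding of patients and research staff without limit, but patients can be blinded only to real versus sham acupuncture (A vs B), and both comparisons with metformin are unblinded to patients and to the doctor who assigns treatment

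*Protocol article*

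**What the plan says.** All references are to the protocol article.

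- **Blinding (2.11):** "In this study, patients, research staff, and data statisticians will be blinded to the assignment". One exception follows: "However, acupuncture therapists cannot be masked as sham acupuncture will be practiced differently from real acupuncture". The claim is not restricted to any pair of groups.
- **Limitations (Discussion):** the same single exception is given as the blinding limitation, namely that "the blinding method cannot be completely used for the acupuncture therapist".
- **Interventions (2.6):** Group A is "SWJQD combined with acupuncture for 3 months", Group B is "SWJQD combined with sham acupuncture for 3 months", and the third arm reads "Group C: Metformin at a dose of 500 mg 3 times/day for 3 months". The only sham or dummy described anywhere is the needling in Group B (2.6.3).
- **Allocation (2.10):** participants are first said to be allocated by an investigator. The random number in its sealed envelope is then "assigned by a staff, who will not be a member of the clinical trial team and participating in data collection". Finally, once a participant is enrolled, "the doctor will open the envelopes in sequence and assign participants to the corresponding intervention accordingly".
- **Comparator (2.2):** the stated purpose is to compare decoction plus acupuncture with metformin.

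**The concern.** An unqualified statement that patients and research staff are blinded will be read as covering all three contrasts. The treatments differ visibly between metformin and the other two arms, and nothing in the plan disguises that difference. The comparison that the study design section puts first would then be reported as patient-blinded when it is not.

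This affects how results are read. The FG score is a clinical rating, and adverse reactions are gathered by investigators who contact participants weekly (2.7.2). Both can be influenced by knowing the treatment. The Discussion also cites blinding as one of the measures that protect the trial from bias, so readers would give the metformin comparison credit that the design does not earn.

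**Working it through.** No published figure is at issue, so the check sets the sections side by side.

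**1. What each participant can observe (2.6 to 2.6.4)**

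| Group | Decoction | Needling | Metformin |
|---|---|---|---|
| A | yes, twice daily outside menses | real | none, no dummy |
| B | yes, twice daily outside menses | sham | none, no dummy |
| C | none, no placebo | none, no sham | oral, stepped up, then three times daily |

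A and B differ only in the needling, for which a sham is described. C differs from both in the form of the medicine, in the dosing times and in the absence of needles. Section 2.9 says the study design is explained before consent, so a participant can be expected to recognise whether or not she is in C.

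**2. Contrast by contrast**

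- A vs B: patient blinding is possible. Women enrolled: 27 + 27 = 54.
- A vs C: patient blinding is not possible. Women enrolled: 27 + 27 = 54.
- B vs C: patient blinding is not possible. Women enrolled: 27 + 27 = 54.

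Two of three contrasts fall outside the claim. Every one of the 81 women contributes to at least one of those two.

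**3. Staff**

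In 2.10 the doctor opens the envelope and assigns the treatment, so that doctor knows the arm. In 2.6.1 a traditional Chinese medicine doctor prescribes the decoction, so the prescriber knows at least that the woman is not in C. Neither role is listed as an exception in 2.11 or in the Discussion.

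Section 2.10 also describes allocation or assignment by an investigator, by a staff member outside the trial team, and by the doctor. It does not say how these roles relate. Investigators also record the weekly adverse reactions (2.7.2). The article therefore leaves open whether someone who allocates also collects safety data.

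**4. Which outcomes are exposed**

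- *Primary (2.7.1):* HOMA-IR and the oral glucose tolerance test. By the formula in 2.4, HOMA-IR is fasting insulin × fasting glucose / 22.5. Both inputs are assays, with no subjective rating. Knowledge of the arm can reach them only indirectly, through behaviour, adherence or drop-out.
- *Secondary (2.7.2):* the FG score and adverse-reaction reports are directly exposed.
- *Analysis (2.11, 2.13):* statistician blinding is stated twice, and nothing in the design contradicts it.

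**The case against.** The strongest reply is that the consequences are limited. The primary outcomes are measured in a laboratory, the statistician is blinded, randomisation and sample size are untouched, and the most exposed outcomes are secondary. All of that stands, and it limits what can be claimed. It does not make the blinding sentence true.

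A second reply is that an article condenses the full protocol. That would excuse a missing detail. Here the article makes a positive statement, names one exception and describes the sham needling at length, and its own arm definitions contradict the statement.

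A reader might go further than the documents allow in five ways:

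- *That the metformin comparisons are open-label throughout.* The text shows that patients and the assigning doctor know the arm. It does not show that laboratory staff or the statistician do.
- *That no research staff are blinded.* The term is undefined. One doctor learning the allocation does not establish that outcome assessors or data staff learn it.
- *That the primary outcomes are biased, or that drop-out will differ by arm.* Section 2.8 gives only an overall 20% allowance (0.20 × 27 = 5.4 women per group) and says nothing about differences between arms. No figure supports a size or direction of bias.
- *That three different people hold the allocation role.* The investigator and the doctor may be the same person, and the outside staff member may only prepare the envelopes. The wording needs reconciling, but a conflict is not proved.
- *That concealment is broken.* Opening sealed, opaque envelopes in sequence after enrolment does not in itself breach it.

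**Conclusion.** The point holds. The blinding claim in Section 2.11, and the matching limitation in the Discussion, are wrong as written for A vs C and B vs C. Patients can be blinded only within A vs B (54 of the 81 women). The two contrasts with metformin are unblinded to patients and to the doctor who opens the envelope and assigns treatment.

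The direct consequence is for adverse-reaction reports and the FG score. Any effect on HOMA-IR or the glucose tolerance test would be indirect, and its size cannot be calculated from the document.

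The conclusion rests on two assumptions: that no placebo decoction, dummy metformin or sham needling for Group C exists beyond what the article describes, and that participants can tell a decoction with needling from oral metformin without it. It does not depend on any view about which other staff are blinded.

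**What to change.** 1. **Section 2.11:** limit the patient-blinding claim to real versus sham acupuncture (A vs B). State that A vs C and B vs C are not blinded to patients or to the staff who assign and prescribe treatment.
2. **Section 2.11:** state which outcome assessors are actually blinded, in particular for the FG score and adverse reactions, and claim no more than that. At present only the statistician's blinding is both stated and uncontradicted, so blinding of other roles should be written in only where it is truly in place.
3. **Section 2.10:** reconcile the roles of the investigator, the outside staff member and the doctor, and say which of them allocates and which opens the envelopes.
4. **Discussion:** add the unblinded metformin comparisons to the limitations, and describe conclusions from A vs C and B vs C accordingly.

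These are changes of wording. Treatments, sample size and analysis stay as they are. The price is a less favourable blinding statement. If the sponsor chooses to introduce blinded assessment that does not yet exist, or to move the opening of envelopes to another person, that would take staff time, which the document gives no means of costing.

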### Data collection and management

2.12

Case report forms (CRFs) will be used to document detailed information related to the study, such as the identity of the participants, clinical information, and any other data collected for the study. The medical records will be kept strictly confidential, input and stored in a password-protected electronic database. The database data and source documents will be checked by a member of the study team not involved in the data collection. The hard copies of all CRFs and clinical data will be stored in a fixed locker for the study team only.

### Statistical methods

2.13

The data of all participants will be involved in the final statistical analysis according to the intent-to-treat principle. The data statisticians will be blinded to the group allocation. All statistical analyses will be performed in SPSS software v19.0 and a *P* value <.05 will be considered statistically significant.

The continuous variables, such as participants’ biochemical and hormonal profiles including estradiol, luteinizing hormone, follicle-stimulating hormone, prolactin, testosterone, progesterone, dehydroandrosterone, sex hormone binding globulin, body mass index, waist-to-hip ratio, FG score, ovulation rate, clinical pregnancy rate, and early abortion rate will be presented as mean ± SD. Between-group comparisons will be carried out on changes from baseline to after treatment using ANOVA or its non-parametric equivalents. Group comparisons will be carried out using the Kruskal-Wallis test followed by Mann-Whitney *U* test.

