### Exclusion criteria

2.5

The exclusion criteria for the participants consist of:

(1)Presence of abnormal liver and kidney functions(2)Presence of any other endocrine disorders such as:(a)uncorrected thyroid disease(b)type 1 or 2 diabetes mellitus or hypertension(c)Cushing's syndrome(d)Congenital adrenal hyperplasia(e)Suspected androgen-secreting adrenal or ovarian tumor.(3)History of alcoholism, malignant tumors, epilepsy, or mental disorders.(4)History of coronary heart disease, severe arrhythmia, cardiopulmonary insufficiency, or cardiac stenting procedure.(5)Use of a pacemaker, hearing aid, or any other device with electronic or metal components.(6)Presence of infectious diseases and severe skin lesions.(7)Pregnant or lactating state.(8)Unable to cooperate with the research caused by other diseases or reasons;(9)Use of hormonal or other medication including Chinese herbal prescriptions, which may affect the outcome of the last 2 months.(10)History of receiving acupuncture treatment in the past 2 months.

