#### Secondary outcomes

2.7.2

(1)Sex hormone profile, including estradiol, luteinizing hormone, follicle-stimulating hormone, prolactin, testosterone, progesterone, dehydroandrosterone, and sex hormone binding globulin levels measured on the 2nd to 3rd day of menstruation, before and after the intervention.(2)BMI (weight/(height)^2^); waist-to-hip ratio (waist circumference/hip circumference), and FG score measured before and after the intervention.(3)Ovulation rate in every menstrual period.(4)Clinical pregnancy rate, and early abortion rate in the 9 months follow-up.(5)Complete genome sequencing of each group before and after the treatment.(6)Security index tests, including routine blood, liver function, kidney function, and blood lipid tests respectively before and after the intervention.(7)Investigators will contact subjects weekly by WeChat message or phone call to record the adverse reactions and side effects in this trial.

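### Clinical pregnancy and early abortion rates are treated as continuous variables with mean ± SD, and the unit of analysis for ovulation is not defined

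*Protocol article*

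**What the plan says.** Section 2.13 of the protocol article opens its list with "The continuous variables, such as participants’ biochemical and hormonal profiles including estradiol" and ends it with the statement that "ovulation rate, clinical pregnancy rate, and early abortion rate will be presented as mean ± SD". Two sentences on testing follow directly:

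- The first sets a comparison of change scores: "Between-group comparisons will be carried out on changes from baseline to after treatment using ANOVA or its non-parametric equivalents".
- The second names rank tests and is silent on change: "Group comparisons will be carried out using the Kruskal-Wallis test followed by Mann-Whitney".

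The threshold for significance is set by the phrase "value <.05 will be considered statistically significant".

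The outcomes themselves are defined in Secondary outcomes (2.7.2). One item reads "Clinical pregnancy rate, and early abortion rate in the 9 months follow-up" and another reads "Ovulation rate in every menstrual period". The Exclusion criteria (2.5) include "Pregnant or lactating state".

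**The concern.** A woman either has a clinical pregnancy in the follow-up or does not, and a pregnancy either ends in early abortion or does not. The natural report is a count over a stated denominator, with a difference between groups and its confidence interval. The article instead assigns these outcomes a variable type and a summary that do not fit them. This is a positive statement, so a fuller analysis plan could repair it only by contradicting the article.

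Four things are at stake for these secondary outcomes:

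- The ± SD carries no information.
- Mean ± SD with a rank test or ANOVA gives no risk difference and no interval for it.
- The denominator of the early abortion rate is open.
- Pairwise rank tests on rare events rest on a poor approximation.

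Ovulation has a different problem. It is observed repeatedly in each woman, and the article does not say whether the analysis unit is the woman or the cycle.

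**Working it through.** **Inputs.** Section 2.8 gives 21 evaluable women per group and 27 enrolled to allow for 20% drop-out. This reproduces: 21 / 0.80 = 26.25, rounded up to 27, and 3 × 27 = 81. The article gives no expected event counts, so every count below is an assumption for illustration.

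**1. The SD adds nothing.** For a 0/1 variable with proportion p, SD = √(p(1 − p)).

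| p (assumed) | mean ± SD |
|---|---|
| 0.05 | 0.05 ± 0.22 |
| 0.10 | 0.10 ± 0.30 |
| 0.20 | 0.20 ± 0.40 |
| 0.30 | 0.30 ± 0.46 |

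The second figure follows from the first in every row. With an assumed 5 pregnancies in 27 women, the planned summary is about 0.19 ± 0.40. The useful report is 5/27 = 18.5%, exact 95% CI 6.3% to 38.1%.

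**2. The change score.** No woman is pregnant at entry, so for pregnancy change = outcome − 0 = outcome. The subtraction is redundant. It also ends at the wrong time: the change sentence runs to after treatment (3 months), while pregnancy and early abortion are counted over the 9-month follow-up. Early abortion has no baseline value, because it exists only for women who conceive during the study.

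**3. The early abortion denominator.** Assume 3 pregnancies and 1 loss among 27 women. Per woman the rate is 1/27 = 3.7%; per pregnancy it is 1/3 = 33%. The article does not say which is meant. The two also answer different questions, because the second compares subgroups formed after randomisation.

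**4. The three-group test hardly moves.** On 0/1 data the tie-corrected Kruskal-Wallis statistic equals (N − 1)/N times Pearson's chi-square, here 80/81 = 0.988.

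- Assumed 2, 4 and 8 of 27: chi-square 4.836, p = 0.089. Kruskal-Wallis 4.836 × 80/81 = 4.776, p = 0.092. ANOVA p = 0.091.
- Assumed 5, 2 and 1 of 27: chi-square p = 0.165, Kruskal-Wallis p = 0.168.

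**5. The pairwise test can move.** Assume 0 of 27 against 5 of 27.

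- Chi-square = 54 × (27 × 5)² / (27 × 27 × 5 × 49) = 984,150 / 178,605 = 5.510.
- Mann-Whitney, normal approximation: 5.510 × 53/54 = 5.408, z = 2.33, p = 0.020 (0.021 with continuity correction).
- Fisher's exact test: 2 × C(27,5) / C(54,5) = 2 × 80,730 / 3,162,510 = 0.051.

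On 0/1 data with equal groups, the exact permutation p-value of the Mann-Whitney test is the Fisher p-value. So 0.021 is an approximation to 0.051, and the two lie on opposite sides of the article's threshold.

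**6. Ovulation.** Recording in every menstrual period gives several yes/no values per woman. Three readings are open: whether she ever ovulated, her fraction of ovulatory cycles, or all cycles pooled. The second is a coarse bounded proportion (with an assumed 3 cycles it can only be 0, 1/3, 2/3 or 1). The third ignores clustering within a woman unless the model allows for it. The entry criteria admit women with long cycles or amenorrhoea, so the number of observed cycles will differ between women.

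**The case against.** The case for leaving this alone has five parts.

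- **The change sentence does not name these outcomes, and the Kruskal-Wallis sentence does not mention change at all.** This stands as an ambiguity. The team may have meant a rank test on the outcome itself. The listing as continuous with mean ± SD is wrong under either reading.
- **The stated test can be run.** This stands for pregnancy. A reader might infer that the analysis is impossible or that its p-values are generally invalid. Step 4 shows otherwise: the three-group p-value shifts by about 0.003.
- **Fisher's exact test is conservative, so part of the gap in step 5 is its caution.** This is fair. The example shows that the approximation can be poor with rare events, not that every pairwise result would be wrong.
- **Ovulation can be averaged.** A per-woman fraction of ovulatory cycles is a legitimate quantity and could have a baseline. A reader might infer that all three outcomes are one yes/no event per woman. Section 2.7.2 does not support that for ovulation, where the fault is the undefined unit.
- **A condensed article may leave methods for categorical data to a fuller plan.** Agreed. The absence of a named categorical method carries no weight here; the point rests on what the article states.

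Wide intervals with few events are also not a consequence of the misclassification. They would remain after the correction.

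**Conclusion.** The point holds for clinical pregnancy and early abortion as a stated misclassification, and for ovulation as an undefined unit of analysis. The consequences are an uninformative SD, no risk difference with an interval, an early abortion rate that may mean 3.7% or 33% on the same assumed data, and pairwise p-values that can be too small when events are rare (0.021 against 0.051 in the assumed example). All event counts are assumptions; only the group size of 27 and the 0.05 threshold come from the article.

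A reader might take this as a threat to the trial's main conclusion. The documents do not support that. These are secondary outcomes, and neither the HOMA-IR and glucose tolerance outcomes nor the sample size depends on them. The point should be fixed before analysis and is not a reason to hold the trial.

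**What to change.** In section 2.13, remove ovulation, clinical pregnancy and early abortion from the list of continuous variables and add one paragraph:

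- **Clinical pregnancy:** report n/N (%) with 95% CI, where N is all women randomised to the group. Compare groups by risk difference with a score-based 95% CI and by Fisher's exact test.
- **Early abortion:** report per woman randomised and per clinical pregnancy, naming each denominator, with exact 95% CIs. Treat the per-pregnancy figure as descriptive, since it is not a comparison of randomised groups.
- **Ovulation:** analyse ovulatory cycles out of observed cycles per woman, with a repeated-binary model (GEE or mixed logistic) or a binomial model that allows for clustering within woman. State the observation window and how a woman with no menstrual period in it is counted.
- **Comparisons:** use the same pairs of groups as for the other outcomes, and take no change from baseline for pregnancy or early abortion.

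The cost is one paragraph of wording. No new data, visits or participants are needed.

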### Inclusion criteria

2.4

The inclusion criteria for the participants are as follows:

(1)Chinese women aged 18 to 35 years.(2)Body mass index (BMI) between 24 to 32 kg/m^2^.^[23,24]^(3)Traditional Chinese medicine syndrome differentiation: kidney deficiency, phlegm and blood stasisness.(4)Satisfying the Rotterdam PCOS diagnostic criteria in adults, including at least 2 of the 3 biochemical or clinical hyperandrogenism characteristics^[25,26]^: (a) Irregular cycles and ovulatory dysfunction (an intermenstrual interval >35 or <21 days or <8 cycles per year) or amenorrhea (>90 days for any 1 cycle), (b) clinical and/or hyperandrogenism: Clinical hyperandrogenism on the Chinese Mainland: Ferriman-Gallwey (FG) score ≥5^[27,28]^; biochemical hyperandrogenism: total testosterone (T) >2.6 nmol/l and free testosterone ≥6.0 pg/ml,^[29]^ (c) polycystic ovarian morphology (the threshold for PCOM should be on either ovary, a follicle number per ovary of >20 and/or an ovarian volume ≥10 ml, ensuring no corpora lutea, cysts or dominant follicles are present.(5)Presence of IR. The criteria of IR is defined by the homeostatic model assessment (HOMA-IR) index ([fasting serum insulin (μU/ml) × fasting blood glucose (mmol/l)] / 22.5). A value ≥2.14 is considered to be indicative of IR.^[30]^(6)No birth planning in the future 3 months.(7)Being able to follow the plan of treatment, examination, and follow-up.(8)Being able to fully understand and voluntarily sign informed consent.

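### The efficacy comparison is an unadjusted change from baseline: a valid test, but less precise than adjusting for the baseline value the trial already collects

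*Protocol article*

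**What the plan says.** The Statistical methods section (2.13) of the protocol article fixes the estimator: "Between-group comparisons will be carried out on changes from baseline to after treatment using ANOVA or its non-parametric equivalents". The sentence after it reads "Group comparisons will be carried out using the Kruskal-Wallis test followed by Mann-Whitney" *U* test, with no condition and no named variable. Neither sentence mentions a baseline covariate or a transformation.

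The Primary outcomes section (2.7.1) names HOMA-IR and the Oral Glucose Tolerance Test (OGTT). HOMA-IR is measured before entry, because the Inclusion criteria (2.4) require insulin resistance: "A value ≥2.14 is considered to be indicative of IR". The Sample size calculation (2.8) arrives at 21 evaluable participants per group "using a 5% significance level, 90% power, and current knowledge of the average serum insulin level", and then enrols 27 per group to allow for drop-out. It gives no difference, SD or correlation.

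**The concern.** A change score subtracts the whole baseline value, which amounts to assuming that follow-up moves one for one with baseline. When the true slope is below 1, the subtraction over-corrects and adds noise to the arm comparison. A slope below 1 is what one expects here, because the measure is imperfectly repeatable and women are selected for being above a threshold. ANCOVA estimates the slope from the data instead of fixing it at 1, and its residual variance is smaller.

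At stake is precision: wider confidence intervals and lower power than the same blood samples could give. The Discussion itself lists the small sample as a limitation. A second, smaller matter is that the article does not say what decides between ANOVA and the rank tests.

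**Working it through.** **The plan's own figure.** The drop-out step reproduces: 21 / (1 − 0.20) = 26.25, rounded up to 27 per group and 81 in total. The 63 evaluable cannot be reproduced or refuted, since no difference or SD is given. Back-solving 21 per arm at two-sided 5% and 90% power implies a pairwise standardised difference of about 1.03 (t-test).

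**Inputs.** From the documents: 21 evaluable per arm, entry cut 2.14. Assumed, because the documents give no figures: HOMA-IR log-normal before the cut with log-mean ln 3 and log-SD s = 0.5, and an underlying correlation r between log baseline and log month-3 values of 0.3, 0.5 or 0.7.

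**Step 1, without the entry cut (equal variance at both visits).**
- Var(change) = 2s²(1 − r)
- Var(ANCOVA) = s²(1 − r²)
- Ratio = (1 + r)/2 = 0.65, 0.75, 0.85

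This overstates the gain here, because the cut shrinks the baseline variance.

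**Step 2, effect of the cut on baseline variance.**
- Standardised cut: a = (ln 2.14 − ln 3)/0.5 = (0.761 − 1.099)/0.5 = −0.676
- λ = φ(a)/[1 − Φ(a)] = 0.3175/0.7504 = 0.423
- Fraction of baseline variance kept: k = 1 + aλ − λ² = 1 − 0.286 − 0.179 = 0.535

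**Step 3, ratio with the cut.** The residual variance s²(1 − r²) is unchanged. The change score adds (1 − r)²ks². Hence

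Var(ANCOVA)/Var(change) = (1 − r²)/[(1 − r²) + (1 − r)²k] = (1 + r)/[(1 + r) + (1 − r)k].

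| r | Ratio | 21 per arm works like |
|---|---|---|
| 0.3 | 1.3/(1.3 + 0.7 × 0.535) = 0.78 | 21/0.776 = 27.0 |
| 0.5 | 1.5/(1.5 + 0.5 × 0.535) = 0.85 | 21/0.849 = 24.7 |
| 0.7 | 1.7/(1.7 + 0.3 × 0.535) = 0.91 | 21/0.914 = 23.0 |

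Setting k = 1 returns the step 1 formula. Simulation under the same assumptions gave the same ratios.

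**Step 4, cost of the covariate.** Estimating one slope at N = 63 raises the variance by about 1/58, or 2%. The equivalent sizes become 26.6, 24.3 and 22.6 per arm, so the range of about 23 to 27 is unchanged.

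**Step 5, what this means for power.** If 21 per arm gives 90% power for a pairwise t-test on log change, the step 3 ratios give ANCOVA about 96%, 94% and 92%.

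**Sensitivity to the assumed distribution.** With median 3.5 and log-SD 0.45, k = 0.657 and the ratio is 0.74 at r = 0.3 and 0.90 at r = 0.7.

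**Simulated trials.** 3,000 trials per cell, 21 per arm, log-normal HOMA-IR with median 3.5 and log-SD 0.45 before the cut, and a log effect of 0.35 in one arm. Three-group power:

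| r | ANOVA, raw change | Kruskal-Wallis, raw change | ANOVA, log change | ANCOVA, log |
|---|---|---|---|---|
| 0.3 | 0.46 | 0.49 | 0.64 | 0.76 |
| 0.5 | 0.57 | 0.60 | 0.75 | 0.84 |
| 0.7 | 0.80 | 0.85 | 0.94 | 0.96 |

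Only the step between the last two columns is due to baseline adjustment. The rest comes from the log scale and presupposes log-normal data. With no effect, rejection rates were 0.04 to 0.056 for every method.

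**The case against.** The strongest reply is that the planned test is legitimate, so preferring ANCOVA is an improvement and not the correction of an error. That stands: type I error is held, and under randomisation the change-score contrast is unbiased over repeated trials. It is also true that no correlation, SD or distribution is documented. The gain is therefore a range under assumptions, and right skew of HOMA-IR is plausible for a product of insulin and glucose but not shown. The reply does not remove the point, because the section states the less efficient estimator explicitly while the covariate is already in hand.

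Three stronger readings are tempting and are not supported.

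- **Contradictory methods.** A reader might take the two sentences in 2.13 as conflicting. Kruskal-Wallis is the rank counterpart of one-way ANOVA, so the second sentence can simply spell out the non-parametric option in the first. What remains is a choice without a stated rule. An analysis plan that is not shown may supply one, and blinding of the statisticians limits the harm.
- **Bias.** Chance imbalance in baseline HOMA-IR does carry into a change-score contrast in the particular trial where it occurs. That is a conditional statement and does not make the planned analysis biased.
- **Drop-outs cannot be included.** Section 2.13 says "The data of all participants will be involved in the final statistical analysis according to the intent-to-treat principle", while 2.8 allows for 20% drop-out. The handling of missing month-3 values may sit in the full protocol or analysis plan. Stopping treatment also need not mean a missing sample, and ANCOVA needs the month-3 value just as a change score does.

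**Conclusion.** The concern holds as a matter of efficiency. Section 2.13 fixes an unadjusted change-from-baseline comparison that is valid but less precise than adjustment for baseline. On the log scale, with the 2.14 entry cut, the ANCOVA variance is about 0.78 to 0.91 of the change-score variance. This rests on an assumed log-mean of ln 3, log-SD of 0.5 and underlying correlation of 0.3 to 0.7. The lower the correlation, the larger the gain; close to 1 it vanishes. The larger ratios of 0.65 to 0.85 should not be used for this trial, because they assume equal variance at both visits and the entry cut breaks that.

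The ratio compares like with like (log change against log ANCOVA) and does not by itself measure the loss from raw changes or rank tests. The absence of a rule for choosing between ANOVA and ranks is a minor point that the same fix resolves.

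**What to change.** Name one primary analysis: ANCOVA of month-3 log HOMA-IR on arm and log baseline HOMA-IR, reporting between-arm ratios of geometric means with 95% confidence intervals. Use the analogous baseline-adjusted model for OGTT glucose values, which 2.7.1 also makes primary, and for the other truly continuous outcomes that have a baseline value. Ovulation, pregnancy and early abortion rates should not go into this model, although 2.13 lists them among the continuous variables. Keep Kruskal-Wallis and Mann-Whitney as a stated sensitivity analysis, which also removes the open choice of test.

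The cost is a change of wording. Baseline HOMA-IR is already needed for eligibility, so the HOMA-IR model needs no new data. The downsides are one degree of freedom (about 2% of variance at 63 women) and effects expressed as ratios instead of differences in HOMA-IR units. The change does not settle missing month-3 values or multiplicity across the two primary outcomes and the arm contrasts; those need their own provisions.
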